In addition to medical therapies, adjunctive non-pharmacologic interventions must be considered whenever applicable for pain in CKD patients undergoing dialysis. Suboptimal pain control is associated with poor QoL, depression, and possibly long-term survival. Nonetheless, adequate medical pain control remains a challenge due to the potential for drug-induced complications and abuse and dependence. Clinicians and the research community should promote pain management in CKD patients undergoing dialysis as a clinical and research priority to improve their QoL and pain-related disability.

Recent studies have shown that novel neuromodulating techniques can have pain-relieving effects in the treatment of chronic pain [9–11]. Studies using anodal transcranial direct current stimulation (tDCS) of motor cortex (M1) or dorsolateral prefrontal cortex (DLPFC) have shown an improvement in pain and depression in several chronic pain syndromes [9]. Anodal tDCS has been shown to increase cortical excitability, promoting pain relief through indirect effects on pain-processing regions in the brain [12]. Promising results have been reported for pain in several diseases such as fibromyalgia, neuropathic pain, chronic post-stroke pain, low back pain, and pelvic pain [9].

tDCS emerges as a simple potential tool to improve QoL and functionality and shed light on the role of brain reorganization in pain function. For CKD patients with chronic pain, tDCS may represent an important cost-efficient, non-pharmacological treatment for a large number of patients with permanent chronic pain, depression, and disability. We currently have no evidence from randomized controlled clinical trials on the use of tDCS to treat pain and depression in CKD patients undergoing HD.

The primary objective of the current study is to evaluate the effects of anodal tDCS over M1 and DLPFC on pain in CKD patients undergoing HD. The secondary outcomes are to assess its impact on depression, anxiety, physical performance, and QoL.

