### Sample size

Sample size was estimated based on statistical considerations for a parallel trial and on previous studies that have paired noninvasive stimulation with chronic pain syndromes [9, 10, 15]. No previous studies have reported results about tDCS using a visual analog scale (VAS) or numeric rating scale (NRS) in CKD. G-Power 3.1.9.2 was used to calculate sample size. VAS is a 0–10-point scale and will be used as the primary outcome. Sample size calculation assumed a significance of 0.05 and power of 0.80. Fregni suggested in previous studies that a mean reduction of 3 points in VAS for the group under active stimulation was expected in contrast to no improvement in the sham group [15]. Sample size was estimated based on the assumption of significance of 0.05, power of 95%, with 0.40 effect size. According to this methodology the sample size would be 36 participants. We decided to add nine more patients to prevent any reduction of power in case of patient dropout. Thus, 45 patients will be recruited and randomized into three groups of 15 patients each.

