**Fig. 2 Fig2:**
[figure not shown]
Illustration of electrode replacement. **a** M1 group. The anodal electrode will be placed over the motor cortex and the cathode over the supra-orbital contralateral area (C3/Fp2 montage). **b** DLPFC group. The anodal electrode will be placed over the DLPFC and the cathode over the supra-orbital contralateral area (F3/Fp2 montage). Electrodes will the placed according to 10/20 EEG international system. Electrode size 35 cm^2^ with a current density of 0.057 mA/cm^2^

During the baseline period, patients will be randomized at a ratio of 1:1:1 to receive sham tDCS (sham group), active tDCS of the primary motor cortex (M1 group), or active tDCS of the left DLPFC (DLPFC group). The M1 was chosen because studies show that stimulation of this area is associated with pain improvement [9, 11, 15, 16]. The left DLPFC was chosen because several studies with neuromodulation have shown that stimulating this area is associated with improvement of depression and also induces an analgesic effect in fibromyalgia [9, 15]. The electrodes will be placed into a 35 cm^2^ square sponge immersed in saline solution (150 mMols of NaCl diluted in water Milli-Q). For stimulation, a gradual current ramp-up and ramp-down with 30-s duration will be used. Electrodes attached to the scalp will be supported by an elastic band. The electrodes (anode and cathode) will be connected to a battery-powered (9 v) stimulator with current verified by a precision digital multimeter (DT832, WeiHua Electronic Co., Ltd, China) with standard error of ±1.5%.

For ethical reasons, no changes will be made to HD routines (days and the place of sessions), clinical care (medicines, imaging, or blood exams), and previous prescription of painkillers or other medication.

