### Statistical analysis

Statistical analyses will use SPSS (v.19.0, Chicago, USA) and Graph Pad Prism 5. Clinical and sociodemographic characteristics (marital status, income, education, and ethnicity) will be described by means and standard deviations for continuous numeric parameters, and by frequency tables with 95% confidence intervals for categorical parameters. Chi-squared test will compare the distributions of categorical variables. Kruskal-Wallis test and ANOVA will compare differences in final values between groups.

The Shapiro-Wilk and Levene’s test will assess the normality of the distribution and homogeneity of variance of the data, respectively. Non-parametric tests will be used in case of non-normality distribution. Mauchly’s test of sphericity will be used to validate the correlation of the repeated measures and where the assumption of sphericity is violated, the Greenhouse-Geisser correction will be applied. The effects of stimulation on primary and secondary outcomes will be calculated using a mixed ANOVA model. The dependent variable will be the score of each outcome, and the independent fixed variables will be the time of treatment (baseline, tenth day, first follow-up, and second follow-up), the group of stimulation (active and sham), and the interaction term time vs group. Post-hoc comparisons will be carried out using Bonferroni correction for multiple comparisons.

Friedman test will be used for non-parametric data. Missing data will be treated by intention-to-treat analysis, taking into account the method of the last observation carried forward. Partial η^2^ will be calculated as measures of effect size in the ANOVA results (main effects and interaction effects). Partial η^2^ will be used to calculate the effect size, where η^2^ = 0.01 will be considered small, η^2^ = 0.06 moderate, and η^2^ = 0.14 large effect. Statistical significance will be set at *p* value less than 0.05.

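### The mixed ANOVA lists its group factor as two levels, active and sham, in a three-arm trial whose primary objective names M1 and DLPFC; the wording should be corrected to three levels

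*Protocol article*

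**What the plan says.** All references are to the protocol article.

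- **Model (Statistical analysis).** One model is named for the treatment effect: "The effects of stimulation on primary and secondary outcomes will be calculated using a mixed ANOVA model". Its factors are then listed with their levels in brackets. Time has four, "the time of treatment (baseline, tenth day, first follow-up, and second follow-up". The group term reads "the group of stimulation (active and sham), and the interaction term time vs group", which is two levels.
- **Arms (Sample size, Randomization method, Intervention).** Patients are "randomized into three groups of 15 patients each". Blocks of six place two patients in each group. Allocation is 1:1:1 to sham, M1 or left DLPFC, and a separate rationale is given for each active site.
- **Objective (end of Background).** "The primary objective of the current study is to evaluate the effects of anodal tDCS over M1 and DLPFC on pain" in this population.
- **Other tests (Statistical analysis).** Kruskal-Wallis and ANOVA are planned for final values between groups, and post-hoc comparisons use a Bonferroni correction. Neither sentence lists the groups or pairs to be compared.

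**The concern.** The stated levels of the group factor conflict with the design. This is not a detail left for a fuller document: the article does give the levels, and they do not match the arms.

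A two-level factor has one between-group contrast at each time, the average of the active patients against sham. It cannot give an M1 effect or a DLPFC effect, and Bonferroni post-hoc tests on it cannot recover them. The Discussion says that the trial is meant to guide a larger multicentre study. A positive result from the two-level model would not tell that study which electrode placement to use. The mismatch also leaves two different analyses, pooled and three-arm, both open to being called the planned one once results are known.

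**Working it through.** **1. What each coding can estimate.** Write a for the mean VAS benefit of M1 over sham and b for that of DLPFC over sham, at a given time. With 15 patients per arm:

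- Two levels (30 active, 15 sham): the group contrast is (15a + 15b)/30 = (a + b)/2.
- Three levels: a, b and a − b can each be estimated.

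The Sample size section expects a 3-point VAS reduction under active stimulation and none under sham. If a = 3 and b = 0, the two-level contrast is (3 + 0)/2 = 1.5 points. The same 1.5 arises from a = 0 and b = 3, or from a = b = 1.5, so the model cannot tell these cases apart.

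**2. Degrees of freedom at N = 45, four times.** For time by group, df = (k − 1)(4 − 1) and (45 − k)(4 − 1).

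- k = 2: (3, 129).
- k = 3: (6, 126).

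The two codings are different tests, so the wording matters if it is followed.

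**3. Does the plan's own sample size settle which was meant?** The stated inputs are effect size 0.40 (read here as Cohen's f), alpha 0.05 and power 0.95, giving 36. The test family and the correlation rho between repeated measures are not stated. Noncentral F calculations for four times give 36 under:

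- three groups, interaction, rho = 0;
- three groups, between-groups effect, rho = 0.1;
- two groups, between-groups effect, rho = 0.2.

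The figure of 36 therefore fits either group structure and decides nothing.

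**4. Power of the two approaches.** The article gives no SD, so standardised effects are assumed. These are two-sided t tests at a single time with a common SD, not the planned interaction over four times. The noncentrality is d × √(n1·n2/(n1 + n2)).

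- One site against sham, d = 1.0, 15 against 15: 1.0 × √7.5 = 2.74 on 28 df. Power is 65% at alpha 0.025 (two contrasts) and 58% at 0.05/3 = 0.0167 (all three pairs).
- Pooled, one site at 1.0 SD and the other at 0: d = 0.5, 0.5 × √10 = 1.58 on 43 df. Power is 34% at 0.05.
- Pooled, both sites at 1.0 SD: 1.0 × √10 = 3.16. Power is 87%.
- Pooled, sites at 1.0 and 0.5 SD: d = 0.75, 0.75 × √10 = 2.37. Power is 64%.

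| True effects (SD) | Pooled, 0.05 | Better site vs sham, 0.025 | Better site vs sham, 0.0167 |
|---|---|---|---|
| 1.0 and 0 | 34% | 65% | 58% |
| 1.0 and 0.5 | 64% | 65% | 58% |
| 1.0 and 1.0 | 87% | 65% | 58% |

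At 1.2 SD the pattern is the same. With one site working, pooled power is 46% against 81% for that site at 0.025. With both working equally, it is 96% against 81%.

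**The case against.** The strongest reply is that the bracketed words are a loose description of the type of stimulation, and that three groups were always meant. Much of this stands. Kruskal-Wallis and ANOVA are the usual choice for three or more groups. A Bonferroni correction has little to do between groups when there is only one contrast, although it could still apply across the four times. Elsewhere in the article, group means one of the three named arms. Bonferroni comparisons over three groups would include each site against sham, and a journal article may leave the naming of pairs to a fuller document, so the absence of named contrasts is no fault in itself.

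The reply does not remove the mismatch. The time factor in the same sentence has its levels listed exactly, so the group list reads naturally as its levels too. The Kruskal-Wallis/ANOVA sentence concerns final values, is not the model assigned to the effects of stimulation, and as an omnibus test would not isolate a site.

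Two stronger readings are tempting. A reader might infer that the sponsor plans to pool the active arms, so that the trial cannot meet its primary objective. The article nowhere says so, and the signs above point to three groups. A reader might also infer that pooling loses power in general. It does when only one site works. With effects of 1.0 and 0.5 SD the two approaches are about equal at alpha 0.025, and with equal effects pooling is stronger. The Intervention section gives an analgesic rationale for both sites, so the one-site case cannot be presumed.

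**Conclusion.** The point holds as a specific error of wording in the main model: two group levels are stated where the design has three. It is probably shorthand. Followed literally, it would yield only the mean of the two site effects (1.5 points in the one-site example) and leave the site-specific objective unanswered.

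The structural conclusion rests on the text alone. The 1.5-point figure uses the article's own 3-point expectation and equal arm sizes. The power figures rest on assumed effect sizes, a common SD and a single time point, and they favour neither approach throughout. This is a correction that should be made before unblinding; it is not evidence that the analysis is planned wrongly.

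**What to change.** In the Statistical analysis section, change the levels of the group factor to M1, DLPFC and sham. Add a sentence stating that the Bonferroni-corrected comparisons include M1 against sham and DLPFC against sham, and that any pooled active-against-sham comparison is secondary.

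This needs no more patients, visits or data. If three groups were always meant, it changes no planned test. The cost arises if both sites work about equally: each site-specific test then has less power than the pooled one (65% at 0.025, or 58% at 0.0167, against 87% at 1.0 SD). That is the price of an answer for each site. The choice of adjusted alpha, of a single primary time point, or of VAS alone as primary outcome goes beyond this correction and is for the trial team to decide.

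### The printed power is not the power of M1 versus sham or DLPFC versus sham, and post-hoc Bonferroni over all three pairs would spend error on a comparison outside the primary objective

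*Protocol article*

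**What the plan says.** The Background of the protocol article states the aim: "The primary objective of the current study is to evaluate the effects of anodal tDCS over M1 and DLPFC on pain". Patients are allocated 1:1:1 to M1, DLPFC and sham.

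The Sample size section gives the power twice. First: "Sample size calculation assumed a significance of 0.05 and power of 0.80". Then: "Sample size was estimated based on the assumption of significance of 0.05, power of 95%, with 0.40 effect size". The software is named, but the test family, the type of effect size and the correlation between visits are not. The section arrives at 36 patients and adds nine for dropout, giving 45, or 15 per arm. It expects a 3-point VAS reduction under active stimulation and none under sham, and prints no SD. It mentions no contrast with sham and no division of alpha.

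The Statistical analysis section plans a mixed ANOVA with time (four levels), group and their interaction, and then: "Post-hoc comparisons will be carried out using Bonferroni correction for multiple comparisons". It does not say how many comparisons are corrected, whether they require a significant overall test, or which visit decides. It describes the group factor as active and sham, although there are three arms.

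**The concern.** Whether M1 works and whether DLPFC works are answered by two contrasts with sham. The sizing refers to neither, so a reader of the Sample size section could take 80% or 95% as the chance of detecting each montage's effect. An overall test can be significant while only one montage, or neither, is shown to differ from sham.

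The default family for post-hoc Bonferroni with three groups is all three pairs. That tests each pair at 0.05/3 = 0.0167 and gives a third of the error to M1 versus DLPFC, which the objective does not ask about. With 12 to 15 patients per arm, that power may matter. The Discussion says the trial is meant to guide a larger multicentre study, and the per-montage answers would inform the choice of montage there.

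**Working it through.** **Inputs from the protocol article.** Alpha 0.05; power 0.80 and 95%; effect size 0.40; 36 patients (12 per arm) before dropout and 45 (15 per arm) recruited; expected difference 3 VAS points; four time points.

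**Assumptions.** The 0.40 is Cohen's f; tests are two-sided; variances are equal and the error is pooled; Bonferroni covers three pairs; SD ranges from 1.5 to 3.0.

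**1. Reproducing 36.** For a group-by-time interaction with 3 groups, 4 times, correlation 0 and epsilon 1, the noncentrality is f² × N × 4 = 0.16 × 36 × 4 = 23.04, with 6 and 99 degrees of freedom. Power is 0.958, and 36 is the smallest balanced total that reaches 0.95. The zero correlation is not printed; at 0.5 the total would be 21. A one-way three-group ANOVA with f = 0.40 does not give 36: it needs 66 for 0.80 and 102 for 0.95. Two other unprinted settings of a between-groups repeated-measures test also give 36. All of these are overall tests, and none is a contrast with sham.

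**2. Effect size per contrast.**
- *Between-group reading.* If both active arms differ from sham by d, the SD of the three means is d√2/3. Setting this to 0.40 gives d = 0.849.
- *Interaction reading.* If the effect is the same at all three post-treatment visits and in both active arms, f = 0.40 gives a difference of 1.96 SD. For 3 VAS points this implies an SD of 3/1.96 = 1.53.

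**3. Power of one sham contrast.** Noncentral t with noncentrality d√(n/2) and 3n − 3 degrees of freedom. Each cell shows 12 per arm / 15 per arm.

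| Effect at one visit | Unadjusted 0.05 | Bonferroni, 3 pairs | Bonferroni, 2 contrasts | Dunnett |
|---|---|---|---|---|
| f = 0.40 between groups (d = 0.849) | 0.52 / 0.62 | 0.34 / 0.44 | 0.40 / 0.51 | 0.42 / 0.52 |
| 3 points, SD 3.0 | 0.66 / 0.76 | 0.48 / 0.60 | 0.55 / 0.66 | 0.56 / 0.67 |
| 3 points, SD 2.5 | 0.81 / 0.89 | 0.66 / 0.78 | 0.72 / 0.83 | 0.73 / 0.84 |
| 3 points, SD 2.0 | 0.95 / 0.98 | 0.87 / 0.94 | 0.90 / 0.96 | 0.91 / 0.96 |
| 3 points, SD 1.5 | 1.00 / 1.00 | 0.99 / 1.00 | 0.99 / 1.00 | 0.99 / 1.00 |

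Under the interaction reading with zero correlation, a contrast on change from baseline at one visit is noisier than one on the final value. Its power is 0.80 / 0.90 with three pairs and 0.85 / 0.93 with two contrasts.

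**4. Share due to the correction.** In the first row the shortfall from 0.80 is 46 points at 12 per arm and 36 at 15. The unadjusted contrast is already 28 and 18 points short. The overall one-way test itself has only 0.53 and 0.64. Dunnett recovers 8 points in each case. Against 95%, the unadjusted contrast is already 43 of 61 points short at 12 per arm and 33 of 51 at 15.

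**5. Overall power is not contrast power, even where 36 is reproduced.** Suppose DLPFC has half the M1 effect, under the interaction reading with zero correlation. In simulation the interaction test has power 0.96 / 0.99. DLPFC versus sham, tested on one-visit change at 0.0167 after a significant interaction, has 0.30 / 0.39.

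**The case against.** The strongest reply is that Bonferroni after an ANOVA is valid and conservative, that keeping M1 versus DLPFC in the family is a legitimate choice in a three-arm trial, and that the count of comparisons can be left to an analysis plan. The first two points are fair. The three-pair family is an assumption here, and the cost estimate depends on it. The mismatch with the sizing does not depend on it: the article fixes both the sizing alpha and the use of Bonferroni, and gives power for neither sham contrast.

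Two stronger readings are tempting, and the documents support neither.

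- *The plan corrects twice, so unadjusted pairwise tests after a significant overall test would do.* The article states no such gate. The closed-test result for three groups holds for one outcome at one time, whereas the plan has three post-treatment visits and two primary pain measures (VAS and MPQ). In a simulation of the four-visit layout, with the interaction as gate and only M1 effective, unadjusted tests of DLPFC versus sham over the three post-treatment visits gave a false DLPFC claim in 11 to 14% of trials. The rate was 5% at a single visit. Three-pair Bonferroni held it at 4 to 5%.
- *Bonferroni leaves per-arm power far below the printed figure.* The 0.34 and 0.44 need a one-visit between-group reading of f = 0.40, which does not reproduce 36. Under the interaction reading that does, each contrast has about 0.8 to 0.9 or more when both montages work equally. Even under the unfavourable reading, most of the shortfall from the printed power is present before any correction or would remain under Dunnett.

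**Conclusion.** The point holds in a limited form. The primary question rests on two sham contrasts, the sizing appears to refer to an overall test at an undivided 0.05, and neither 0.80 nor 95% is the power of M1 or DLPFC versus sham.

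If Bonferroni covers all three pairs, the avoidable loss against Dunnett is about 8 points per contrast for a one-visit between-group f of 0.40. It is about 7 points (12 per arm) or 5 (15 per arm) for 3 VAS points with SD 2.5, and close to nil for final values with an SD near 1.5. The printed effect size cannot settle which applies, because its type, the SD and the correlation are not given. This is a matter of efficiency and of reporting power correctly, not of inflated error: Bonferroni as planned is conservative.

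**What to change.** **Statistical analysis section.** For the primary pain outcome at one named visit, state that M1 versus sham and DLPFC versus sham are tested with Dunnett's test, or with Bonferroni over these two contrasts only (0.025 each). Label M1 versus DLPFC secondary. The two-contrast Bonferroni gives up about one point of power to Dunnett and carries over directly to the planned non-parametric fallback. The 5% family-wise guarantee then applies to one pain measure at one visit. It does not by itself cover VAS and MPQ together, or several visits. Do not substitute unadjusted pairwise tests after a significant overall test.

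**Sample size section.** State which test the printed power refers to, and give the power of each sham contrast under the chosen rule at 12 and 15 per arm, with the SD or correlation assumed.

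**Cost.** A sentence or two in each section, and no extra patients. M1 versus DLPFC loses confirmatory status, though the objective does not ask for it. The stated per-arm power may be less favourable than 0.80 or 95%.

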To assess the flexibility of the lower limbs (posterior thigh muscles), a sit and reach test will be performed. A chair 43 cm high and 50 cm of backrest will be used. During the test, participants will be instructed to sit on the edge of the chair with feet flat on the floor, knees and ankles at 90° flexion; then the dominant or painful leg will be stretched (hip and knee) with the calcaneus supported on the floor and with the ankle flexed at 90°. With overlapping hands and middle fingers on the same level, participants try to get as close as possible to their toes and hold that position for 2 s in three attempts, to get the arithmetic mean. A negative score will be recorded if the middle fingers do not reach the toes, and a score will be positive if the middle fingers were above the toes. Flexibility of the upper limbs will be performed using the scratch flexibility test. Participants will be instructed to pass one hand (dominant or more painful) over the shoulder to assess flexibility of the shoulder in flexion, abduction, and external rotation and to try to reach the other hand to assess extension, adduction, and internal rotation on the center of the back. Three replicates will be made to obtain the arithmetic mean of the results. The measurements will be made using a ruler, and the scores are considered negative if there is any distance between the middle fingers, and positive if the middle fingers overlap.

Timed Up and Go (TUG) test will be used to measure, in seconds, the time taken to stand up from a standard chair, walk 3 m, turn, walk back to the chair, and sit down. A chair with armrests and a seating depth of 44–47 cm is recommended [22]. Those who complete the test in less than 20 s tend to be independently mobile, able to get in and out of a chair without assistance, and climb stairs. The TUG test score correlates well with measures of gait speed, functional ability, and balance. An improvement of 1.4 s on the TUG test (within-patient change score) has been identified as the minimum clinically important difference [22].

The Kidney Disease Quality of Life—Short Form (KDQOL-SF) will be used to assess the QOL. This questionnaire is a specific instrument to evaluate patients on dialysis, applicable to all types of dialysis [23].

A total score for each physical test will be described by means and standard deviations. A total score of variables and all subscales will be compared within and between groups.

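### If normality fails, the fallback for the mixed ANOVA is Friedman's test, which has no group factor and cannot test the group or group-by-time effect

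*Protocol article*

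**What the plan says.** All of this is in the protocol article. The Background sets the primary objective, to "evaluate the effects of anodal tDCS over M1 and DLPFC on pain in CKD patients undergoing HD", and the design is sham-controlled, so the question is one of differences between arms.

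Under Statistical analysis, "The effects of stimulation on primary and secondary outcomes will be calculated using a mixed ANOVA model". Its fixed terms are four assessment times, "the group of stimulation (active and sham), and the interaction term time vs group". Normality is checked by Shapiro-Wilk, and "Non-parametric tests will be used in case of non-normality distribution". After the paragraph on the mixed model comes the only rank method named for repeated measurements: "Friedman test will be used for non-parametric data".

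One other rank test appears in the same section: "Kruskal-Wallis test and ANOVA will compare differences in final values between groups". The end of Outcome measures adds: "A total score of variables and all subscales will be compared within and between groups". Nothing states which result carries the conclusion when the rank tests are in use.

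**The concern.** The mixed ANOVA and its replacement answer different questions. The interaction term asks whether the arms change differently over the four visits. Friedman's test asks whether scores differ between visits within one set of patients. Pooled over arms, it ignores randomisation. Run arm by arm, it yields three separate p-values, none of which compares active stimulation with sham.

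Improvement in every arm is plausible here. Entry requires a VAS pain score above 4 (Inclusion criteria), which invites regression to the mean, and a sham response may add to it. A test of change over time will pick up that shared improvement. The rule covers the primary outcome and every secondary one. The Discussion says the trial is meant to guide a larger multicentre study, so a misread result would carry forward.

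**Working it through.** **Inputs from the protocol article.** Three arms of 15 (Sample size), four assessments and alpha 0.05 (Statistical analysis), VAS scored 0 to 10 (Sample size).

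**Assumed, because the article gives no figure.** SD 2 at each visit, correlation 0.5 between visits, normal scores, and any improvement fully present at all three post-baseline visits.

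**The plan's own figure.** The only related figure is the pre-dropout sample size of 36. Treat it as a within-between interaction with k = 3 arms, m = 4 visits, f = 0.40 and correlation 0:
- noncentrality = f² × N × m / (1 − ρ) = 0.16 × 36 × 4 / 1 = 23.04
- df1 = (k − 1)(m − 1) = 6 and df2 = (N − k)(m − 1) = 33 × 3 = 99
- power = 0.958, and N = 36 is the smallest balanced size reaching 0.95

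So 36 is consistent with sizing for the interaction that the fallback drops. It does not prove this: a correlation of 0.5 gives 21, and other settings also give 36. The present point changes no sample-size figure.

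**What each test responds to.** Rejection rates at 0.05, 4,000 simulated trials per row:

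| True state | Friedman, pooled | Friedman, per arm (sham / M1 / DLPFC) | Mixed-ANOVA interaction | Kruskal-Wallis, last visit |
|---|---|---|---|---|
| All arms improve by 2 (no treatment effect) | 100% | 92.5 / 92.1 / 91.2% | 4.6% | 5.1% |
| One arm 3 points apart at every visit, no change over time | 4.6% | 4.8 / 5.1 / 5.0% | 5.2% | 98.2% |
| M1 −2, DLPFC +2, sham 0 | 2.2% | 4.7 / 91.9 / 91.8% | 100% | 99.6% |
| Both active arms −3, sham 0 | 100% | 4.6 / 99.8 / 100% | 99.7% | 98.0% |

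Pooled Friedman gives the same answer in the first and last rows, where the treatment effect is respectively nil and large. It misses opposite changes that cancel (third row). A constant difference between arms drops out (second row) because ranking is within patient.

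**If per-arm Friedman results were compared informally.** Let p be the chance that one arm is significant when all arms follow the same course. With independent arms and q = 1 − p:

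P(sham not significant, at least one active arm significant) = q × (1 − q²) = q − q³

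- No change: p about 0.046, so 0.954 − 0.954³ = 0.954 − 0.868 = 0.086.
- Common improvement of 2 points: p about 0.92, so 0.08 − 0.08³ = 0.079.
- Maximum at q = 1/√3 = 0.577: 0.577 − 0.192 = 0.385. Under these conditions the rate cannot exceed about 38%, whatever the SD or correlation.

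Simulation agrees (baseline mean 6.5, scores clipped to 0–10, 3,000 to 4,000 trials per setting):

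| Common improvement (points) | 0 | 0.5 | 1.0 | 1.5 | 2.0 | 2.5 |
|---|---|---|---|---|---|---|
| An active arm significant, sham not | 8% | 18–19% | 36–38% | 27–29% | 8–9% | 1% |

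**With Kruskal-Wallis alongside.** At 0.5, 1.0 and 1.5 points it rejected in 4–5% of trials. The misleading Friedman pattern together with a significant Kruskal-Wallis occurred in about 1.0%, 1.9% and 1.4%. At 1.0 point, about 34 of the 36 percentage points arose while Kruskal-Wallis was correctly non-significant. The two rank tests would then point different ways, with no rule to settle it.

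**How often the fallback is reached.** The article does not say what Shapiro-Wilk is applied to. With perfectly normal data and independent tests, any rejection among 12 arm-by-visit cells has probability 1 − 0.95¹² = 46%; among four visit-level tests, 1 − 0.95⁴ = 19%. Both figures also assume that one rejection triggers the switch.

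**The case against.** The best defence is that the article already names a between-group rank test. Read with the statement that scores are compared within and between groups, the non-parametric path could be Friedman within arms and Kruskal-Wallis between them. Comparing final values is valid in a randomised trial without baseline adjustment, though less efficient. In the simulations Kruskal-Wallis held its 5% level and had about 98% power for a 3-point difference. The mixed ANOVA also remains the main analysis, and a condensed article may leave the pairing of rank tests and contrasts to an analysis plan.

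Much of this stands, and it rules out three stronger readings. A reader might infer that no between-group test remains after the switch; the Kruskal-Wallis sentence says otherwise. A reader might infer that the trial will judge efficacy by significance in an active arm and its absence in sham; no sentence says so. A reader might take the 38% as the trial's false-positive rate. It is the rate of an informal reading that the article does not adopt, at its least favourable point, and it comes from simulated trials not restricted to those failing normality.

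What does not fall is the choice of method. The section gives Friedman as the test for non-parametric data in the analysis of stimulation effects, and Friedman cannot supply the group or group-by-time test. That is a stated method unsuited to its purpose, not a detail left out. Kruskal-Wallis on final values does not replace the interaction, since it uses neither baseline nor the other visits.

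**Conclusion.** The point holds in a limited form. On the non-parametric path the plan loses its group and group-by-time tests over the four visits, keeps a valid but narrower comparison at one time point, and does not say which result decides. The loss of the group factor is a property of Friedman's test and rests on no assumption. The size of the possible misreading rests on several: that within-arm results are read as treatment evidence, that all arms share the same course, and the SD and correlation given above. The main parametric analysis is unaffected. This should be corrected before analysis, but it does not undermine the trial.

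**What to change.** Remove Friedman as the fallback for the treatment effect. Keep the between-group model for every outcome and check its residuals. If they are clearly non-normal, test the same active-versus-sham contrasts by permutation of treatment labels, or by rank ANCOVA on follow-up scores adjusted for baseline. State that this between-group result decides. Report within-group changes descriptively only, without using their p-values as evidence of efficacy.

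The cost is a few sentences of wording and a little programming. Design, recruitment, assessments and sample size do not change.
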